## Methods/Design

A multi-centre, randomized, evaluator-blinded, two-group parallel design will be adopted, comparing the impact of the Beyond Silence (CBE) program with mental health literacy training. A parallel group design will be adopted where participants in both groups will receive 12 hours of group-based education, but the content, schedule and format will be different. The 1:1 randomization sequence will be generated off site (in Calgary) using the software Stata. Randomization will occur in four blocks of 26 and four blocks of 24, leading to n = 100 in each assignment group and exactly 12 or 13 participants in each assignment. The sequence will not be shared with the investigative team, who will instead determine each participant’s assignment using an interactive web-based system. Mental Health First Aid training (MHFA) will serve as the control group since its efficacy is already well established in the literature [32]. The “Beyond Silence” approach is novel, and based on best practice principles, but research is needed to determine whether it is effective. Help seeking/outreach behavior, mental health literacy, and mental health stigma will be assessed at 3 month intervals: at baseline, after completion of the program and at 3 months follow-up. The study protocol was registered in May 2014 on ClinicalTrials.gov (ID#: NCT02158871). Ethical approval was also obtained through the Hamilton Integrated Research Ethics board.

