### Participants

The study will be conducted in two healthcare organizations in the same mid-sized urban center in southern Ontario. One is a large healthcare facility that employs approximately 10,000 full and part-time workers across five sites. The other organization is a mid-sized hospital with approximately 4000 employees across three main sites. Volunteer participants will be recruited through posters, staff newsletters, intranet sites, information sessions with program managers, and email follow-up. Inclusion criteria include: a) full, part-time or casual employment in any area of the organization, b) agreeable to being randomly assigned to either of the two programs, c) commitment to attending the 12 hours of mental health education outside of paid work time, and d) no prior training in either program. Screening will be completed by the project coordinator either via email or by telephone. Recruitment and random assignment to the two groups will continue over four intake periods in each organization, according the sample justification outlined below. Consent will be obtained from each participant prior to completion of the each online survey (pre, post and at 3-month follow-up), with a hard copy of the consent form provided at the start of the first in-person session.

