The plan is to enroll 200 employees in total, with 100 participants in each group. In each of the four intake periods, we plan to include 24 to 26 participants, and will actively recruit to ensure sufficient numbers prior to randomization. Following randomization, an intent-to-treat analysis will be incorporated, including all study participants. Quantitative precision estimates suggest that this sample size is sufficient to detect any real and important benefit of CBE over literacy training on change in help-seeking behavior. Two RCT evaluations of MHFA (literacy) interventions among Australian healthcare workers found that 50% to 75% of workers reportedly offered help to a person with mental health problems, prior to the intervention [24,25]. Based on this, we expect an average of about 1–2 behaviors at baseline across the samples. To simplify, we approximate the precision to detect change in mean count from baseline to the 6 month follow-up using calculations for the linear mixed-effects model, but allowing for non-constant variance of the counts by assuming that the variance averaged over groups and occasions might be as high as 4. Also assuming high consistency of help-seeking within groups (test-retest correlation, 0.80), we have an 80% chance of finding a significant (p < .05) difference between the two groups in average change over 6 months of as little as 0.44 behaviors. That is, even if the real advantage of CBE over MHFA is very small (less than 1 new behavior, on average), we have a high probability of detecting it. The precision for estimating mediators such as changes in stigma scores is similarly high. Based on initial pilot data, there were significant increases in behavior over time therefore the projected sample size should be more than sufficient to detect change.

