The control group intervention is Mental Health First Aid (MHFA), a standardized, twelve-hour educational program designed to teach participants how to recognize the early warning signs of mental illness, how to provide initial help to someone in a mental health crisis, and how to support people who are developing mental health problems [25]. It is an evidence-based approach, with several RCT’s documenting significant increases in mental health literacy, decreased social distance, and increased reports of helping behaviors [24,34,35]. The program originated in Australia, but is being implemented across Canada, under the leadership of the Mental Health Commission of Canada. A staff member in each organization who has been trained through the 5-day instructor-training program will be seconded to facilitate the program within their organization. Each course will be offered as two full days, typically one week apart. All participants will receive a training manual, which covers all of the content of the standardized, module-based curriculum. Over the course of the project, eight courses will be offered with approximately 12–13 participants per course.

The location and specific dates/times for the sessions will be customized for each group in order to facilitate participation and maximize response rate, but groups will scheduled to start in regular intervals over the course of the two years (fall, winter, spring, fall). The Beyond Silence programs will be scheduled in the early evenings (outside of regular work hours), and the MHFA programs will be scheduled for two full days, one week apart.

Monthly meetings will be scheduled with the peer educators to provide support, address any questions/concerns, and maximize fidelity to the principles of the Beyond Silence program. A fidelity measure was designed to track adherence to structural elements (6 items), as well as content and process principles (10 items) of the program, using a 4-point Likert-type rating scale. Fidelity assessment will occur between sessions 3 and 5, and will be completed by a participant observer who is part of the core project team. Ratings will be discussed with peer educators at monthly meetings, with any departures from the established principles noted and explained, including plans (if applicable) to improve adherence. Fidelity to the MHFA program principles will be monitored through MHFA Canada, as per their internal processes.

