### Data analysis

In accordance with Research Question 1, we hypothesize that help-seeking behavior will increase from baseline to 3 and 6 months by a greater amount in the Beyond Silence group than in the MHFA control. The primary approach to this question is the repeated measures analysis of a checklist of desirable help seeking/help providing behaviors, obtained from the survey at each time point. Overall tests of the change across all three measurements are available from generalized linear mixed-effects analysis, assuming that the count (from 0 to 20 behaviors) is distributed as a Poisson variable. This is a standard approach that accounts for over-dispersion in the Poisson model arising from the repeated measurements, permits the inclusion of participants who have not completed all three assessments, and allows for flexible modeling of the change over time and the inclusion of any relevant covariates [41]. In the primary analysis, the statistical significance of treatment group in this model will be used to address the first research question. In view of the randomized design, the primary analysis will not include additional covariates, but the model will be used to explore modifying effects by including additional covariates (e.g. age, sex, prior experience with mental illness) and interactions between these covariates and treatment group. As a secondary outcome, we will analyze a scaled measure of behavioral intentions using similar linear mixed-effects analysis.

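### The trial randomizes in eight balanced blocks, but the primary model leaves block out, so the precision that blocking can give is not credited to the standard error (minor)

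*Protocol article*

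**What the plan says.** All places are in the protocol article.

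- **Methods/Design** sets the allocation: "Randomization will occur in four blocks of 26 and four blocks of 24, leading to n = 100 in each assignment group". Each block holds 12 or 13 participants per arm.
- **Participants** describes recruitment: "Recruitment and random assignment to the two groups will continue over four intake periods in each organization". There are two organizations. The same section gives the intake size: "In each of the four intake periods, we plan to include 24 to 26 participants".
- **Interventions** plans eight Beyond Silence programs and eight MHFA courses of about 12 to 13 people each, with groups "scheduled to start in regular intervals over the course of the two years (fall, winter, spring, fall").
- **Data analysis** specifies a Poisson mixed model over three measurements and tests treatment group in it. On covariates it says: "In view of the randomized design, the primary analysis will not include additional covariates". Age, sex and prior experience with mental illness are named as examples of covariates for exploring effect modification. Block, organization and intake are not named as model terms anywhere, although the section notes that the model can carry covariates.

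**The concern.** The randomized design is offered as the reason for having no covariates. For participant characteristics such as age or sex that is a defensible choice. For the blocking factor the argument runs the other way. Blocking forces the arms to be equal in size within each block, so differences between blocks cannot contribute to the difference between arms. The true sampling variance of the treatment effect is reduced accordingly, but a model without block still counts the between-block variation as error. Its standard error is then larger than the design warrants, the test is conservative, and some power is lost.

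It is plausible that blocks differ in change. Intakes start in different seasons, contact with a co-worker is asked about over the past six months, and the two organizations have about 10,000 and 4,000 employees. The article gives no evidence on how large such differences are.

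**Working it through.** **1. Do the blocks match organization by intake?**
- Blocks: 4 × 26 + 4 × 24 = 200 participants; 4 × 13 + 4 × 12 = 100 per arm.
- Cells: 4 intakes × 2 organizations = 8, equal to the number of blocks.
- Intake size of 24 to 26, read per organization: 8 × 24 = 192 to 8 × 26 = 208, which brackets 200.
- Programs: eight per arm of 12 to 13 people, so one of each kind per block.

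The match is a strong inference. The article does not state it.

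**2. The plan's own detectable difference.** Inputs from Participants: n = 100 per arm, variance 4, correlation 0.80, 80% power, p < .05 (sidedness not stated), detectable difference 0.44. Formula: (z_alpha + z_power) × SD × √(2/100).
- Change from baseline to 6 months, SD = √(2 × 4 × 0.2) = 1.265: two-sided 0.501, one-sided 0.445.
- Mean of the two follow-ups minus baseline, SD = √(4 × 0.2 × 1.5) = 1.095: two-sided 0.434.

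The 0.44 is therefore reproduced by the one-sided change or by the two-sided mean of both follow-ups. The two-sided change from baseline to 6 months gives 0.50. None of these calculations contains a block term. The steps below use the two-sided change and a true difference of 0.50, which has 80% power when blocks do not differ.

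**3. Effect of omitting block.** Let f be the share of the variance in change that lies between blocks. The article gives no value, so f is assumed. Training-group clustering is taken as zero, and a normal approximation stands in for the Poisson mixed model.
- The unadjusted model reports SE = SD × √(2/n). The true SE is that × √(1 − f).
- Standard error too large by the factor 1/√(1 − f).
- Type I error, unadjusted: 2 × [1 − Φ(1.96/√(1 − f))].
- Power, unadjusted: Φ((2.802 − 1.96)/√(1 − f)).
- Power, block fitted: Φ(2.802/√(1 − f) − 1.96).

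| Assumed f | SE too large by | Type I error, unadjusted | Power, unadjusted | Power, block fitted | Gain (points) |
|---|---|---|---|---|---|
| 0% | 0% | 5.0% | 80.0% | 80.0% | 0 |
| 2% | 1.0% | 4.8% | 80.2% | 80.8% | under 1 |
| 5% | 2.6% | 4.4% | 80.6% | 82.0% | 1.4 |
| 10% | 5.4% | 3.9% | 81.3% | 84.0% | 2.7 |
| 20% | 11.8% | 2.8% | 82.7% | 88.0% | 5.3 |

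Unadjusted power also rises with f, because the true standard error shrinks whether or not the model recognizes it. The gain must be taken from that column, not from 80%.

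**4. Simulation check** (eight balanced blocks, 4,000 runs per setting, Gaussian outcomes, difference 0.50). At f = 5%, 10% and 20% of the variance in change, power without and with block was 80.6% and 81.7%, 79.9% and 82.9%, and 81.3% and 86.6%. The pattern agrees with the formulas.

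**5. Block differences in level only** (10% of total variance, same simulation). A test of change had 79.4% power without block and 79.2% with it, so nothing is lost. A test of follow-up level without baseline had 42.1% and 45.2%.

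**The case against.** **Only part of the block variation matters.** Baseline is one of the three measurements, so stable differences between organizations or intakes go into the between-person variance and cancel from a contrast of change. A reader might infer that all block and season variation inflates the error. The documents do not support that: for a test of change, only block-by-time variation does so. Level differences count only if treatment group is tested as a main effect, and the Data analysis section does not say which test is meant. This limits the point but does not remove it.

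**The size is assumed.** No block, organization or season variance is given, and at 2% or less the gain is under one point. This stands.

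**The test may not be conservative overall.** Participants are taught in groups of 12 to 13. If training groups share an assumed 1% to 5% of the variance in change, then at f = 5% the unadjusted variance factor is (1 − 0.05 − 0.01) + 12.5 × 0.01 = 1.065 to (1 − 0.05 − 0.05) + 12.5 × 0.05 = 1.525. The type I error is then about 5.8% to 11%. This stands as a limit on the type I error column, which isolates the effect of omitting block. The article contains no training-group term, and the fix here does not depend on one.

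**The sentence may be aimed at participant characteristics.** The examples that follow it are of that kind, and an analysis plan that is not shown could deal with block. Read as written, however, it excludes every additional covariate and gives randomization as the reason. It is a stated rule, not a detail left open.

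**Conclusion.** The point holds as a minor one. The article randomizes in eight balanced blocks, rules out every additional covariate in the primary model, and justifies this with a feature of the design that argues for fitting block. The consequence is some lost precision. A reader might infer a biased treatment effect; with 1:1 allocation inside every block, omitting block does not cause one.

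At assumed block shares of 5% to 10% of the variance in change, the loss is about 1.4 to 2.7 points of power, and at 20% it is 5.3 points. This rests on the assumed shares, on no training-group clustering, on a normal approximation, and on the inference that blocks are organization-by-intake cells.

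**What to change.** In Data analysis, replace the covariate sentence with: *The primary model includes randomization block (organization by intake, 8 levels) and its interaction with time; no other covariates are included.* In Methods/Design, confirm that the blocks are the organization-by-intake cells.

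The cost is one sentence and 7 block parameters plus 7 × 2 = 14 block-by-time parameters (three measurement occasions), 21 in all. That is minor with 200 participants measured three times. The exploratory covariate analyses can stay as they are.

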The survey will include 6 main sections. Content and data collection methods will be identical in the two groups:**Demographic data** (gender, age, education, ethnicity, job tenure, position) will be gathered to obtain a basic profile of participants.**Mental health experience** – Participants will be asked whether they have a history of mental health issues, either in themselves or a family member (yes/no), the nature of these issues (examples provided), and any personal experiences with mental health issues over the past six months (yes/no). The presence of mental health issues is based on self report, and will be defined as changes in thinking, mood or behavior that impair day-to-day functioning [34]. This lay definition and examples will be provided to capture a range of experiences that may or may not have been formally diagnosed by a medical practitioner.**Help-seeking behavior** – Participants will be asked to report whether they accessed any services from a list of 10 health, workplace and community service options. Questions regarding service utilization are adapted from the 2012/2012 Canadian Community Health survey [36], in order to provide a population reference, although several work-related services (e.g. EAP, union) are added as an option. Participants may endorse more than one of the behaviors, and a summative score of the number of behaviors will be used to measure change in help-seeking. Since the incidence of reported help seeking may be low over the time frame of the study, attitudes or intent to seek help will also be tracked. Intention to seek psychiatric help is a significant predictor of behavior [18]. The Attitudes Toward Seeking Professional Psychological Help Scale–short form (ATSPPHS), a 10 question survey using a four point Likert-type scale response will be used to track beliefs and intent to seek professional help [37]. It is a widely used scale with good internal consistency (α = .78), and criterion validity supported by links between scale scores and mental healthcare use [37].**Outreach behavior** – Baseline and follow-up data will be gathered regarding personal contact with a co-worker about mental health problems (yes/no), and any contact over the past 6 months (yes/no). If contact did occur, participants will be asked whether they provided help to the co-worker, and if so, to identify the type of help from a list of 10 possible options. The list of “outreach” behaviors was based on the ones used for evaluation of the MHFA program (e.g. ‘spent time listening to problem’, ‘recommend professional help’) [34], with an adaptation to include a several work-specific options (e.g., ‘recommend EAP’, ‘offered assistance with job duties’). Participants are invited to check all behaviors that apply (with an open-ended option), and scoring is based on one point per action, with a summative score used to track change. In addition to the behavior list, participants will be asked to rate their confidence in providing help on a 7-point Likert scale.**Stigma towards co-workers with mental illness** – The MHCC Opening Minds Scale for Healthcare Providers will be used; a 20-item questionnaire that was designed to evaluate the attitudes of healthcare providers towards people with mental illness [38]. The tool has good internal consistency (α = .82), and satisfactory test-retest reliability (ICC = .66), with limited impact of social desirability [38]. This tool is being implemented in sites across the country by researchers with the Mental Health Commission Opening Minds team; therefore data from this project can be linked with the larger database.**Mental Health literacy** – Four vignettes of employees with workplace mental health issues will be used to assess awareness of issues and when/how to respond to these issues in the workplace. The vignettes are adapted for a healthcare workplace based on a review of vignettes reported in the literature study [33,39,40], as well as analysis of key issues reported in the pilot phase of the study. Vignettes will incorporate differences in gender, nature and severity of illness, and a 7-point Likert scale from novice to expert will be used to track key dimensions of literacy, including perceived knowledge about the condition, what to say/do and what resources to access [33].

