In Research Question 2, we propose mediating forces that are expected to be different in the two programs, including scaled measures of mental health literacy (expected to be higher in the MHFA group), stigma regarding mental illness (expected to be greater in the Beyond Silence group), and attitudes towards seeking professional help (expected to be higher in the Beyond Silence group). Following recommendations by Baron and Kenny [42], we will initially explore whether changes in literacy occur in association with the interventions. These analyses will use linear regression, modeling change in literacy and stigma, respectively, occurring in association with the interventions. Next, we will use Poisson or negative binomial regression to determine whether changes in literacy, stigma and attitudes associated with intervention (as well as overall levels of each) predict counts on the desirable behavior checklist. If associations are observed in both cases, we will evaluate change in these measures using linear mixed effects as described for Research Question 1. Substantial diminishment, or disappearance, of the effect of the interventions on help-seeking when the potential mediators are included in the model will be interpreted as providing evidence of mediation.

The random assignment of participants to intervention groups eliminates biases in the evaluation of the treatment effects, but the generalizability of this effect in relation to the representativeness of the sample will be assessed by comparing demographic and employment data from study participants to the equivalent data available for the entire organization. This data also provides insight on the reach of the program within the organization in terms of the characteristics of who volunteers to participate in this kind of program. This augments the qualitative analysis of Research Question 3.

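### The first mediation step regresses change in stigma and literacy on program and names no baseline term; adding the baseline score would make a valid test more efficient at almost no cost

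*Protocol article*

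**What the plan says.** The mediation plan is in the protocol article, Data analysis, under Research Question 2. It opens as an exploration: "we will initially explore whether changes in literacy occur in association with the interventions". The model follows: "These analyses will use linear regression, modeling change in literacy and stigma, respectively, occurring in association with the interventions". The method is therefore linear regression, the outcome is change, and the predictor is the intervention. A baseline score is neither included nor excluded.

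The second step regresses the behavior count on the mediators. Here the article does name levels as well as changes: "as well as overall levels of each) predict counts on the desirable behavior checklist". The third step depends on the first two: "If associations are observed in both cases, we will evaluate change in these measures using linear mixed effects as described for Research Question 1".

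Two other places bear on the point. The Data collection section has each participant complete a survey before training, so the baseline mediator scores will be available. The same section reports that the stigma scale has "satisfactory test-retest reliability (ICC = .66") and gives no corresponding figure for the literacy vignettes.

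**The concern.** In a randomized comparison, an unadjusted change score amounts to fixing the coefficient of the baseline score at 1. The efficient coefficient is the correlation between baseline and follow-up when the two variances are equal. With a correlation near .66, a slope of 1 overcorrects and leaves noise in the contrast that the baseline score could remove.

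This matters because step 1 helps decide which mediators go on to the later mixed-effects analysis. Stigma is the mechanism that the contact-based program adds to literacy training, and Research Question 2 asks what mediates its effect. A less precise first step more often misses a real program effect on stigma or literacy, and then the condition for the later step is not met.

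**Working it through.** **Inputs**

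- 100 participants per group (Participants section).
- Correlation r between baseline and follow-up: .66 for stigma, taken from the ICC in Data collection. The retest interval is not stated, so using it over the study interval is an assumption.
- Literacy: no figure given; 0.50 to 0.80 assumed.
- Two-sided 5% test and 80% power for the change-score test: both assumed. The article says only that precision for the mediators is comparably high.
- Equal variances at the two occasions; no dropout.

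**The plan's own figure.** The only stated detectable difference is 0.44 behaviors, for the behavior count, with variance 4 ("assuming that the variance averaged over groups and occasions might be as high as 4") and correlation 0.80 ("Also assuming high consistency of help-seeking within groups (test-retest correlation, 0.80")). A two-sided test of change from baseline to six months gives 2.802 × √(2 × 4 × 0.20 × 2/100) = 0.50. A one-sided test of the same change gives 0.445, and a two-sided test of the mean of the two follow-ups minus baseline gives 0.434. So 0.44 is reached under variants that the text does not name. It concerns another outcome and sets no power for stigma or literacy.

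**Variance, in units of the score variance, at r = .66**

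- Change score: 2(1 − r) = 2 × 0.34 = 0.680.
- Baseline-adjusted: 1 − r² = 1 − 0.4356 = 0.5644.
- Ratio: (1 + r)/2 = 0.83, that is, 17% less.

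**Where the extra variance comes from.** A chance baseline difference of d SD shifts the change contrast by (1 − r)d = 0.34d toward the group with the lower baseline. This adds 0.34² = 0.1156 to the variance, and 0.5644 + 0.1156 = 0.680. Chance imbalance is thus the whole of the excess variance and not a second problem on top of it.

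**Power and detectable difference.** With 1.960 + 0.842 = 2.802:

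- Adjusted power = Φ(2.802/√0.83 − 1.960) = Φ(1.115) = 86.8%, against 80%.
- Detectable difference, change score: 2.802 × √(0.02 × 0.680) = 0.327 SD.
- Detectable difference, adjusted: 2.802 × √(0.02 × 0.5644) = 0.298 SD.

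A simulation of 20,000 trials with t-tests gave 79.8% and 86.5%.

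**Sensitivity to r, change-score power set at 80%**

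| r | Variance ratio | Adjusted power | Gain (points) |
|---|---|---|---|
| 0.50 | 0.75 | 89.9% | 9.9 |
| 0.60 | 0.80 | 88.0% | 8.0 |
| 0.66 | 0.83 | 86.8% | 6.8 |
| 0.70 | 0.85 | 86.0% | 6.0 |
| 0.80 | 0.90 | 84.0% | 4.0 |

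**Sensitivity to starting power, r = .66.** The gain is 7.6 points from 50%, 8.1 from 60%, 7.9 from 70%, 6.8 from 80% and 4.5 from 90%.

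**The case against.** The strongest reply is that the defect is read from silence. A regression of change on program plus baseline also fits the quoted sentence, and it is the very analysis recommended here. The article is condensed, and a covariate list for a secondary question can reasonably sit in a fuller plan. The statement "In view of the randomized design, the primary analysis will not include additional covariates" is limited to the Research Question 1 model and cannot be carried over to this step. All of this stands: a reader might infer that the plan excludes baseline adjustment from step 1, and the text does not say so. What remains is that the article does specify method, outcome and predictor, and names levels only for the second step. Unadjusted change is therefore the natural reading, and the wording should settle it.

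A reader might also infer a loss of 7 points by the plan's own figures. The article supplies only the ICC. The 80% starting power, the two-sided 5% test and the use of the ICC over the study interval are assumptions, and the ICC covers stigma alone.

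Finally, a reader might take chance imbalance and regression to the mean as a bias. Averaged over randomizations, the change-score contrast is unbiased and keeps its type I error. The step is also described as exploratory, and the gain in detectable difference is only about 0.03 SD. These points limit the weight of the concern but do not remove it.

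**Conclusion.** The concern holds as a modest point of efficiency. As described, step 1 compares change between programs without using a baseline score that is already collected. If it is fitted that way, the stigma test has residual variance 1/0.83, or about 1.20 times, that of the adjusted test. This corresponds to about 7 points of power if the change-score test stands at 80% and the baseline to follow-up correlation is .66. For literacy only the assumed range of about 4 to 10 points can be given. A correlation below .66 over the study interval would enlarge the stigma gain; a higher one would shrink it.

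The validity of step 1 is not in question, and the primary behavior analysis is unaffected.

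**What to change.** In the Data analysis section, Research Question 2, state that the step 1 regressions of stigma and literacy include the baseline score of the same scale as a covariate. Either the follow-up score or the change score may serve as the outcome. Because change is follow-up minus baseline, the program estimate is identical and only the baseline coefficient differs, by 1. If baseline adjustment was already intended, the same sentence makes that clear.

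The cost is one sentence and one degree of freedom per model, with no new data.
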